### **Provider survey**

The sample size calculations for the provider survey gives the anticipated level of precision for calculating the proportion of providers that know the treatment guidelines (that is report that parasitological testing is recommended and that ACTs are for confirmed cases of malaria). Based on logistics and costs a total of 138 facilities (an average of three to four facilities per cluster) will be included in the study. From the baseline survey we know that there are three to four workers per facility hence we can expect on average 138 workers to be surveyed per arm. Assuming that the estimate of the primary outcome is 50% in the control arm and 75% in each of the intervention arms, and an intra-correlation coefficient (ICC) of 0.25, this allows us to estimate the true primary outcome with  $\pm 14.5\%$  precision in the control arm and  $\pm 12.5\%$  precision in each of the intervention arms.

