## Methods/design

The interventions will be evaluated using a three-arm stratified, cluster randomized trial across 42 clusters, 14 clusters per arm, in two areas in Nigeria. Since the school-based intervention is being delivered at the community level a cluster is defined as a geographical community which contains at least one facility and one school, and this will be the unit of randomization with study site (urban-rural setting) as the stratum. Clusters will be selected at random within each stratum with the number per stratum selected probability proportional to size. Due to logistics and costs, a total of 138 health facilities and 38 schools will be included in the study. Schools and facilities will be randomly selected from within each cluster to receive the cluster intervention. Up to three schools per cluster will be randomly selected from a list of schools

provided by the Research and Statistics Department of the Ministry of Education Enugu State, while the number of facilities per cluster will be selected probability proportional to size. Communities will be randomized to one of the following three arms:

- Arm 1 (expected standard practice):
  - Facilities invited to supply RDTs
  - Demonstration on how to use RDTs
- Arm 2
  - Facilities invited to supply RDTs
  - Provider intervention: training and supervision on malaria diagnosis and treatment (which includes a demonstration on how to use RDTs)
- Arm 3
  - Facilities invited to supply RDTs
  - Provider intervention: training and supervision on malaria diagnosis and treatment (which includes a demonstration on how to use RDTs)
  - School-based malaria education intervention.

The first arm represents expected standard practice when RDTs are introduced in public health facilities and medicine retailers. This is the approach most likely to be adopted by the State Malaria Control Programme and the Association of Community Pharmacists and Association of PMDs in the near future. All of these organizations have been involved in the design of the interventions. To date, only a small quantity of RDTs has been distributed with basic training to public health facilities in Nigeria. None have been distributed to facilities taking part in this study.

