### **Household survey**

Sample size calculation for the household survey is based on the number of clusters identified for the patient exit survey (that is 14 clusters per arm) and gives the anticipated level of precision for calculating the primary outcome; the proportion of individuals surveyed that know that parasitological testing is recommended and know that ACTs are the recommended treatment for confirmed cases. Assuming that the estimate of the primary outcome is 10% among those attending facilities in Arm 1 (expected standard practice), 20% for those living in clusters receiving the provider intervention (Arm 2), and 50% in the combined provider and school intervention clusters (Arm 3), that one individual per household will be sampled and the intra class-correlation ( $\rho$ ) will be 0.2, we will survey 25 per cluster (350 per arm). This allows us to estimate the true primary outcome with  $\pm 7.9\%$  precision in Arm 1,  $\pm 10.5\%$  precision in Arm 2, and  $\pm 13.1\%$  precision in Arm 3.

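### The provider-survey margins of ±14.5% and ±12.5% do not follow from the stated inputs, and 138 workers per arm is the minimum of the implied range, not its average

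*Protocol*

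**What the plan says.** The design is a "cluster randomized trial across 42 clusters, 14 clusters per arm" (Protocol, Methods/design).

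Under Sample size, Provider survey, the Protocol gives these inputs:
- Facilities: "Based on logistics and costs a total of 138 facilities (an average of three to four facilities per cluster) will be included in the study".
- Workers: three to four in each facility, "hence we can expect on average 138 workers to be surveyed per arm".
- Expected proportions: "50% in the control arm and 75% in each of the intervention arms".
- Clustering: "an intra-correlation coefficient (ICC) of 0.25".

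From these it derives margins of ±14.5% (control) and ±12.5% (each intervention arm).

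Under Sample size, Household survey, the proportions are 10%, 20% and 50% in Arms 1, 2 and 3, the ICC is 0.2, and "we will survey 25 per cluster (350 per arm). This allows us to estimate the true primary outcome" with margins of ±7.9%, ±10.5% and ±13.1%.

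Neither paragraph gives a formula, a confidence level or a correction for the number of clusters.

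**The concern.** The two paragraphs make the same kind of statement, an anticipated half-width for a proportion in one arm of a clustered survey. A reader should be able to get both sets of figures from the listed inputs by one rule. The usual design-effect formula gives provider margins wider than stated and household margins narrower than stated, so the two surveys do not appear to share a rule.

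The provider head count has a separate problem. It is presented as an expected average, but it equals the facility count per arm times three, the lower end of the stated workers per facility.

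What is at stake is limited: whether the precision promised for provider knowledge is correct and reproducible. The primary-outcome calculation for the patient exit survey does not depend on it.

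**Working it through.** **Rule.** Half-width = q × √[p(1−p) × DEFF / n], with DEFF = 1 + (m−1) × ICC and m = n / clusters. I take q = 1.96 (two-sided 95%, an assumption). The cluster is the randomized community, 14 per arm.

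**Provider survey, stated inputs** (n = 138, ICC = 0.25):
- m = 138/14 = 9.86; DEFF = 1 + 8.86 × 0.25 = 3.21.
- Control, p = 0.50: 1.96 × √(0.25 × 3.21/138) = 14.96%, against 14.5% stated.
- Intervention, p = 0.75: 1.96 × √(0.1875 × 3.21/138) = 12.95%, against 12.5% stated.
- Shortfall: 0.46 and 0.45 points (3.2% and 3.6% in relative terms).

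**What would give the stated pair.** With n kept at 138, a margin that rounds to 14.5% needs DEFF between 3.000 and 3.042, and one that rounds to 12.5% needs DEFF between 2.970 and 3.018. Both therefore need DEFF of about 3.0, which at ICC 0.25 means m of about 9. With m = 9 and n = 138 the results are 14.45% and 12.51%. But 14 × 9 = 126, and n = 126 with m = 9 gives 15.1% and 13.1%. Treating the facility as the cluster (46 per arm, m = 3) gives 10.2% and 8.9%, which does not match either.

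**The head count.** 138 facilities / 3 arms = 46 per arm. Then 46 × 3 = 138, 46 × 3.5 = 161 and 46 × 4 = 184.

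| Workers per arm | m | Control | Intervention |
|---|---|---|---|
| 138 | 9.86 | 14.96% | 12.95% |
| 161 | 11.50 | 14.70% | 12.73% |
| 184 | 13.14 | 14.51% | 12.57% |
| Stated | – | 14.5% | 12.5% |

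The margin falls steadily as n rises. Meeting the stated values exactly would take about 186 workers (control) and 196 (intervention), both above the maximum of 184. At 184 the control figure agrees after rounding, but the intervention figure rounds to 12.6%.

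**Household survey** (n = 350, m = 25, ICC = 0.2, DEFF = 1 + 24 × 0.2 = 5.8):
- Plain rule: 7.57%, 10.09% and 12.62%.
- Counting 13 clusters instead of 14 (c−1, n = 13 × 25 = 325): 7.85%, 10.47% and 13.09%. These round to all three stated figures.
- The match is not unique. DEFF = 1 + 25 × 0.2 = 6 with q = 2 and n = 350 gives 2 × √(p(1−p) × 6/350) = 7.86%, 10.47% and 13.09%. The text does not show which rule was used.

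**The c−1 rule applied to providers** (n replaced by n × 13/14, m unchanged): 15.52% and 13.44% at 138, 15.26% and 13.22% at 161, 15.06% and 13.04% at 184. No single variant tried reproduces both surveys.

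**The case against.** The strongest reply is that the discrepancy is trivial. It is under half a point, in a margin that rests on a guessed ICC and guessed proportions, for a survey of secondary outcomes. With the Protocol's own three to four workers per facility it shrinks to about 0.2 points at 161 workers and to less than 0.1 at 184. This stands as to size. It does not make the paragraph correct, because the text names 138 workers and no count in its range yields both figures.

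A reader might infer three stronger points that the Protocol does not support.

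- *The household margins are wrong too.* They are wider than the plain rule gives, so they are conservative, and an ordinary design effect with a one-cluster allowance reproduces all three. The rule is unstated, but the figures are not in error.
- *Every margin is too narrow because a t quantile is required.* On 13 degrees of freedom the margins would be 16.5% and 14.3% (providers) and 8.3%, 11.1% and 13.9% (households). But the Data analysis section prescribes stratified t-tests for comparisons between arms and fixes no quantile for a single-arm precision statement. With two strata one could equally argue for 12 degrees of freedom in one arm or 24 for two. A t quantile is a reasonable option, but leaving it out is not an error.
- *These margins are the only justification of the surveys' size.* The number of facilities is attributed to logistics and costs, and the household survey takes its cluster number from the patient exit survey. For the provider survey in particular, precision is reported as the consequence of a size set on other grounds.

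**Conclusion.** The point holds for the provider survey only, and it is minor. On the stated inputs the margins are about ±15.0% and ±13.0%, so the printed ±14.5% and ±12.5% are too favourable by about half a point. The likeliest explanation is a cluster size of 9 paired with a sample of 138, but that is an inference from the back-calculation. The count of 138 is the minimum implied by the Protocol, not the average.

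The household figures can stand under a c−1 rule. What needs attention is that this rule is unstated and is not the one behind the provider figures.

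The conclusion assumes 95% confidence, the community as the unit to which the ICC applies, and equal cluster sizes. The primary outcome and its sample size are unaffected.

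**What to change.** 1. Correct the expected number of providers per arm. Either give the range 138 to 184 (midpoint 161), or keep 138 and call it the minimum, at three workers per facility.
2. State the formula once for both surveys: confidence level, cluster size, design effect, and whether one cluster is deducted.
3. Restate the provider margins under that rule. To match the household survey (c−1) they are ±15.5% and ±13.4% at 138 workers, or ±15.3% and ±13.2% at 161. Under the plain rule they are ±15.0% and ±13.0% at 138, or ±14.7% and ±12.7% at 161.
4. Leave the household margins as they are if the c−1 rule is adopted. If the plain rule is chosen for both surveys, they become ±7.6%, ±10.1% and ±12.6%.

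The cost is an edit to two paragraphs and slightly less favourable figures for a secondary survey. No change to recruitment or sample size is needed.

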### **Household survey**

Sample size calculation for the household survey is based on the number of clusters identified for the patient exit survey (that is 14 clusters per arm) and gives the anticipated level of precision for calculating the primary outcome; the proportion of individuals surveyed that know that parasitological testing is recommended and know that ACTs are the recommended treatment for confirmed cases. Assuming that the estimate of the primary outcome is 10% among those attending facilities in Arm 1 (expected standard practice), 20% for those living in clusters receiving the provider intervention (Arm 2), and 50% in the combined provider and school intervention clusters (Arm 3), that one individual per household will be sampled and the intra class-correlation ( $\rho$ ) will be 0.2, we will survey 25 per cluster (350 per arm). This allows us to estimate the true primary outcome with  $\pm 7.9\%$  precision in Arm 1,  $\pm 10.5\%$  precision in Arm 2, and  $\pm 13.1\%$  precision in Arm 3.

### **Randomization**

With cluster randomized trials there is an increased chance that the study arms are unbalanced with respect to known and unknown potential confounders, and therefore undermines the credibility of the trial results. Stratified randomization will reduce some of the imbalance in factors known to be correlated with the study outcome and the study site. However, this does not

enable us to balance on type of facility and the number of facilities which were also expected to be important correlates of the primary outcome. Hence, a system of constrained randomization [41,42] will also be used to allocate communities to the study arms within each stratum to ensure balance in these factors.

The validity of the restricted randomization will be assessed by producing a matrix where the rows and columns represent the clusters and the elements of the matrix are the proportion of times each pair of clusters is allocated to the same study arm, that is the probability that the  $i^{\text{th}}$  cluster is being allocated to the same intervention group as the  $j^{\text{th}}$  cluster. The matrix will then be examined for under- and over-represented pairs that would highlight any potential causes for concern in the randomization.

Randomization of the clusters will be performed by the study statistician after informed consent has been sought from the heads of the facilities, community heads, and schools to avoid selection bias. Patients (or caregivers) and fieldworkers administering the patient exit survey will be blinded to group assignment. The research team involved in implementing the interventions and supervising data collection will need to be aware of which clusters and in turn which facilities and schools receive the different interventions (Figure 3).

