### **Sample size**

#### **Patient exit survey**

Sample size calculations are based on the primary outcome; the proportion of febrile patients receiving treatment as recommended in malaria treatment guidelines. Based on provider adherence to test results in our formative research and assumptions about the incentives of providers in private facilities we expect that this will be 10% in the control arm (basic provider training) with a coefficient of variation within stratum of 0.35. Using methods

for stratified cluster randomized trials [40] 14 clusters per arm with a harmonic mean of 50 febrile patients per cluster will be needed to detect a 15% incremental increase between the study arms, from 10% to 25% for the provider intervention (arm 2), and from 25% to 40% with the addition of the school intervention (arm 3) with 80% power at a 5% significance level.

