### **Data analysis**

The primary outcome will be compared between each of the study arms using methods appropriate for cluster randomized trials. Due to the small number of clusters per arm analysis based on cluster-level summaries will be applied. Point estimates of the primary outcome will be calculated using the weighted average of the cluster proportions, with the weights provided by the sample size for each cluster. If the distribution of the summary measures in each study arm is skewed, a logarithmic transformation to the proportions will be considered. An overall estimate of the risk difference will be obtained by taking a weighted average of the stratum-specific estimates with the weights proportional to the number of clusters in each stratum since an equal number of clusters have been allocated to the study arms within each stratum. 95% confidence intervals (CI) will be adjusted for observed between-cluster variance and formal hypothesis testing will be conducted using stratified t-tests. Adjustment for covariates, including patient and provider characteristics and knowledge, contextual factors, and process factors, will be carried out using a two-stage process. In the first stage a logistic regression model including stratum as a fixed effect and the covariates of interest, but excluding the intervention effect, will be fitted to calculate cluster-specific expected values. The difference of observed to expected values will give the

[figure not shown]

difference-residual for each cluster. In the second stage, the above methods are carried out with the cluster-level proportions replaced with the covariate-adjusted residuals.

Secondary outcomes will be analyzed using the methods described above. To examine whether secondary outcomes associated with the patient vary according to urban/rural residence and socioeconomic status methods appropriate for examining an interaction between the intervention and the individual-level variable will be applied [43].

Data will be double entered using Microsoft Access 2007 (Microsoft Inc., Redmond, WA, USA) and analyzed using STATA version 11.0 (STATA Corporation, College Station, TX, USA). A full analysis plan will be reviewed and agreed before the data are analyzed.

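### Allocation is constrained on facility type and number of facilities, but the stated t-test accounts for stratum only, and the planned adjustment neither names these factors nor says which analysis is primary

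*Protocol*

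**What the plan says.** Protocol, Randomization: stratifying by study site does not allow the trial to "balance on type of facility and the number of facilities which were also expected to be important correlates of the primary outcome". Constrained randomization therefore "will also be used to allocate communities to the study arms within each stratum to ensure balance in these factors". How tight the balance must be is not stated.

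Protocol, Data analysis: the analysis uses cluster-level summaries, and the risk difference is a weighted average of stratum-specific estimates. The 95% confidence intervals "will be adjusted for observed between-cluster variance and formal hypothesis testing will be conducted using stratified t-tests". Stratum is the only design factor in this test.

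The same section plans an adjusted version: "Adjustment for covariates, including patient and provider characteristics and knowledge, contextual factors, and process factors, will be carried out using a two-stage process". A first-stage logistic model with stratum and covariates, but without the intervention, gives expected values. In the second stage "the above methods are carried out with the cluster-level proportions replaced with the covariate-adjusted residuals". The constraint factors are not named, and neither analysis is called primary. A full analysis plan is to be agreed before the data are analysed; it is not at hand.

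**The concern.** Constraining the allocation removes most of the chance difference between arms in facility type and number of facilities. If these factors predict the outcome, the arm difference varies less from one possible allocation to another than under stratification alone. The stratum-only t-test takes its standard error from the spread of clusters within arms and strata, and that spread still contains the variation due to these factors. The standard error then describes a design less precise than the one used: intervals are too wide and the test runs below 5%.

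The planned adjustment could repair this, but not as its list stands. Knowledge and process factors arise after randomisation. The provider training aims to raise provider knowledge, the school component aims to raise community knowledge, and the provider survey follows the patient exit survey. Adjusting for such variables may remove part of the effect under study. The two baseline factors that shaped the allocation are the natural covariates, and they go unnamed.

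**Working it through.** **1. The plan's own figure.** Inputs (Sample size, Patient exit survey): 10%, 25% and 40% in the three arms, coefficient of variation k = 0.35 within stratum, m = 50, 80% power, 5% significance (taken as two-sided). The plan states "14 clusters per arm with a harmonic mean of 50 febrile patients per cluster will be needed".

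Clusters per arm = a + (1.96 + 0.84)² × [p0(1−p0)/m + p1(1−p1)/m + k²(p0² + p1²)] / (p1−p0)², with a = 1 (unmatched) or a = 2 (stratified variant).

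- 25% vs 40%: bracket = 0.00375 + 0.00480 + 0.1225 × 0.2225 = 0.03581. Then 7.849 × 0.03581 / 0.0225 = 12.49, so 13.49 (a = 1) or 14.49 (a = 2). Power at 14 clusters is 81.5% or 78.4%.
- 10% vs 25%: bracket = 0.00180 + 0.00375 + 0.1225 × 0.0725 = 0.01443, giving 5.03, so 6.03 or 7.03.

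The 14 per arm is reproduced. Arm 3 vs arm 2 is the binding contrast. The calculation takes no credit for the constraint.

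**2. Size of the effect in closed form.** Take two arms at 25% (the null case). The variance of a cluster proportion is 0.1875/50 + 0.1225 × 0.0625 = 0.00375 + 0.00766 = 0.01141. The standard error of the difference is √(2 × 0.01141/14) = 0.0404. Let R² be the share of within-stratum between-cluster variance that the constraint factors explain. With perfect balance the true variance per cluster is 0.01141 − R² × 0.00766, while the stratum-only test still estimates about 0.01141. Reported SE over true SD is then:

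- R² = 0.2: √(0.01141/0.00988) = 1.07
- R² = 0.4: √(0.01141/0.00834) = 1.17
- R² = 0.6: √(0.01141/0.00681) = 1.29

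These are limits; imperfect balance gives less.

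**3. Simulation.** Three arms of 14 clusters, 50 patients each, k = 0.35, two cluster-level constraint covariates, 6,000 trials per cell, arm 3 vs arm 2. Assumed because the protocol does not give them: R², 9 + 5 clusters per arm in the two strata, and allocation drawn from the best-balanced 10% of stratified allocations. Adjustment was by cluster-level linear regression, a stand-in for the two-stage method (25 df unadjusted, 23 adjusted).

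| R² | SE / true SD, unadjusted | Type I error, unadj. / adj. | Power, unadj. / adj. | 95% CI half-width (points), unadj. / adj. |
|---|---|---|---|---|
| 0 | 0.99 | 4.9% / 5.0% | 82% / 81% | 10.2 / 10.4 |
| 0.2 | 1.07 | 3.7% / 4.7% | 83% / 87% | 10.3 / 9.5 |
| 0.4 | 1.13 | 2.8% / 5.7% | 84% / 93% | 10.4 / 8.7 |
| 0.6 | 1.23 | 1.6% / 5.1% | 86% / 97% | 10.4 / 7.8 |

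Monte Carlo error on a 5% rate is √(0.05 × 0.95/6,000) = 0.28 points. The 5.7% lies about 2.4 of these above 5%, and there is no trend with R².

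With stratification but no constraint, the unadjusted SE ratio stays at 0.99 and type I error at 4.8% to 5.2% for every R². The conservatism therefore comes from the constraint. Adjustment raises power without the constraint too (83% to 85%, 82% to 90% and 81% to 96% for R² = 0.2, 0.4 and 0.6), so the gain is the usual one from using a prognostic covariate.

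**4. Sensitivity to set-up.** A repeat simulation with 42 clusters, two covariates and R² of 0.2 to 0.6 gave an SE about 4% to 25% too large, type I error of about 4% falling to 1.8%, and 3 to 10 points less power. A two-arm version with one covariate, balance within 0.15 SD, strata of 22 and 6 clusters, and the logistic-residual adjustment the protocol describes gave, for R² of 0.3/0.5/0.7, unadjusted type I error of 3.0/1.7/0.8%, adjusted 4.9/5.1/4.8%, and power rising from 84/87/88% to 90/95/98%.

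**The case against.** The strongest reply is that the protocol already contains the remedy. It says the two-stage adjustment will be carried out, and facility type and number could be read into its contextual factors. Nothing in Randomization contradicts Data analysis, and the exact covariate list, the lead analysis and the degrees of freedom are commonly left to the statistical analysis plan, which may settle all three.

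Much of this stands. A reader might infer that the primary test ignores the constraint factors and that adjustment is merely optional. The text supports neither: adjustment is planned, and no analysis is labelled primary. A reader might also infer that the trial falls short of its planned power or risks false positives. The figures show the opposite: the unadjusted test keeps 82% to 86% power in the main simulation and errs on the conservative side.

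What does not fall away is this. The protocol does not leave the analysis blank. It fixes a test and an interval that account for stratum only, and it names covariate categories that include post-randomisation ones while omitting the two factors it randomises by. A plan that followed this text literally would lose efficiency in one analysis and could adjust away part of the effect in the other.

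**Conclusion.** The point holds as an efficiency matter. If facility type and number of facilities are prognostic, as the protocol expects, the stratum-only t-test has an SE about 4% to 25% too large, type I error of about 4% down to 1.6%, and about 3 to 11 points less power than an adjusted test, for an explained share of 20% to 60%. In the main simulation the half-width shrinks by 1 − 9.54/10.29 = 7% at a share of 20% and by 1 − 7.75/10.44 = 26% at 60%. At a share of zero the cost of adjusting is about 1 point of power or less. The gain matters most for arm 3 vs arm 2, the contrast that sets the sample size.

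The direction is firm. The size is not, because the protocol gives neither the explained share nor the tightness of the constraint. The lost power is relative to a better analysis, not to the stated 80%. The finding shows neither bias nor extra false positives in the stratum-only test.

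**What to change.** - Name the pre-randomisation cluster values used in the constraint (facility-type mix and number of facilities), with stratum, as the covariates of the already planned two-stage cluster-level analysis.
- State that this adjusted analysis is primary.
- Reduce the t-test degrees of freedom by the number of cluster-level covariates. For a two-arm comparison with two strata, 28 − 4 = 24 becomes 22 with two covariates.
- Keep provider knowledge, process factors and other post-randomisation variables out of the primary adjustment. If they are of interest, use them only in separately labelled exploratory analyses.
- Report the stratum-only t-test as a sensitivity analysis. A permutation test over the set of acceptable allocations may be added as support.

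The cost is a few sentences in the protocol or analysis plan and about two degrees of freedom. The critical t value moves from 2.064 to 2.074, which is 0.5%. No new data are needed, because the values had to exist for the constrained allocation. The choice should be fixed before the data are analysed.
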